## Adverse events

All adverse events are documented on the sheet provided in the eCRF, regardless of whether they are serious or not, during the noninterventional study including the follow-up phase. For patients who discontinue the treatment prematurely, the adverse events are documented for up to 90 days after treatment discontinuation.

An adverse event is any untoward occurrence in an affected person administered a medication and which does not necessarily have to have a causal relationship with this treatment. These also include the following events:

- Abnormal laboratory values, insofar as they
  - are accompanied by clinical symptoms or
  - result in a change in the treatment (e.g. dose adjustment, interruption of treatment, discontinuation of treatment) or
  - require medical intervention or
  - are considered clinically relevant by the physician
- Special situations, i.e. overdose, abuse, misuse, medication error or near-misses
- Lack of efficacy (LoE) / progression of disease
- Suspected Transmission of Infectious Agent by Medicinal Product (STIAMP)
- Drug interactions
- Product quality and/or technical complaints
- Reports involving suspect counterfeit or counterfeit drugs / falsified medicinal products

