| Duration: | According to the product information, the duration of the combination therapy with ribavirin (Copegus®) for chronic hepatitis C depends on the virus genotype. Naive patients with virus genotype 1 and genotypes 2/3 should be treated for 48 weeks and 24 weeks, respectively. Patients with low viral load at baseline (< 800,000 IU/ml) and Rapid Viral Response (HCV-RNA undetectable after 4 weeks of treatment), can sufficiently be treated for 24 weeks only, in case of genotype 1, and for 16 weeks only, in case of genotypes 2/3.  This recommendation is identical for patients with genotype 4.  Duration of retreatment in patients who have failed prior therapy should be 48 weeks in general. In case of genotype 1 patients with prior non-response, retreatment duration of 72 weeks is recommended.  The recommended duration of Pegasys monotherapy is 48 weeks.  In clinical studies with peg­interferon alfa-2a (Pegasys®) alone or in combination with ribavirin (Copegus®) (see product information), a Rapid Viral Response was defined by a HCV RNA load below the limit of detection after 4 weeks of therapy whereas an early virological response was defined by a HCV RNA load below the limit of detection or by a reduction of the virus titre by 99 % of the initial value after 12 weeks of therapy.  Of patients with genotype 1 or 4 and no early virological response after 12 weeks therapy with peg­interferon alfa-2a (Pegasys®) alone or in combination with ribavirin (Copegus®), only a very small number (<2%) achieved sustained virological response.  In those patients, therapy should be discontinued, taking into account the low probability of a sustained virological response.  In patients with genotype 2 or 3, early virological response is known to be very high (97 %) and subsequently a high SVR rate is achieved after 24 weeks. Therefore, viral load determination after 12 weeks of treatment is not deemed to be necessary.  Planned FPI: 01/01/2008  Planned LPI: 31/12/2011  Planned LPO: 30/06/2013 |

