#### To week 24 of follow-up

- Body weight
- Laboratory parameters
  GPT (=ALT), GOT (= AST), GGT,
  Other laboratory parameters:
  hemoglobin, platelets, WBC, neutrophils (%), bilirubin, creatinine, TSH, blood glucose (fasting), HbA1c, triglycerides, cholesterol, HDL, LDL, serum ferritin ANA, LKM, SMA, AMA, SLA, Trak, MAK, TSH, rheumatoid factors
- Hepatitis C laboratory diagnostic tests
  HCV-PCR (qualitative/quantitative) *only qualitative recommended*
- Hepatitis B laboratory diagnostic tests (only if chronic hepatitis B was documented at the baseline examination): HBsAg (+/-), HBeAG +/-; HBV-DNA quant./qual., anti-HBs (+/-); anti-HDV (+/-), HDV-RNA (+/-, qual. or quant.)
- Adverse events (including suspected cases) with substance-specific causality survey
- Concomitant medication
- Clinical symptoms: none, fatigue, fever, muscular stiffness, skin changes, hair loss, joint pain, muscle pain, abdominal pain, nausea, reflux, weight loss, headache, insomnia, irritability, restlessness, depression, depressive mood, psychosis, impaired concentration, anorexia, jaundice, pruritus, elevated GPT, craving / withdrawal-like symptoms, other treatment-related sick leave (duration) since the last examination
- Pregnancy
- Quality of life assessment compared to before treatment: symptom-free; improved, but not symptom-free; unchanged
- Alcohol consumption no/yes, if yes, inquiry ≤/ > 40 g/d and drinks/d in the last 30 days
- Submission of the SF-36 and sociodemography record form (questionnaire to be completed by the patient)

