## Analysis plan

The descriptive statistical evaluation is performed by the company factum GmbH.

All recorded data – depending on the type of characteristics – are presented descriptively as mean, standard deviation, minimum, maximum, median, 1st and 3rd quartile or their frequency distribution. Categorical characteristics are presented with absolute and relative frequencies within the individual categories.

For continuous variables multiply recorded over time, basic statistics with absolute differences between the end of observation and the baseline value are calculated.

For the tolerability analysis, adverse drug reactions are counted by frequencies using the respective preferred terms categorized according to organ systems. These survey tables are additionally stratified according to the clinical relevance of the drug effect as "serious/non-serious".

Moreover, an assessment of the clinical tolerability of the hepatitis C therapy is performed by the physician.

For the safety laboratory analysis, basic statistics over time are generated per parameter. Additionally, the frequencies of changes in categorical laboratory values (classified into "normal", "increased", "reduced") are presented per laboratory parameter between the baseline value and end of treatment and between the end of treatment and follow-up.

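### Adverse events have a post-treatment window that depends on how treatment ended, and reactions are then tabulated as crude frequencies over 16- to 72-week treatments

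*Protocol*

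**What the plan says.** **When recording ends.** Protocol section 7.4 has all adverse events documented "during the noninterventional study including the follow-up phase", then makes an exception: "For patients who discontinue the treatment prematurely, the adverse events are documented for up to 90 days after treatment discontinuation". In section 7.2.2 the only post-treatment visit is headed "To week 24 of follow-up", and its list contains "Adverse events (including suspected cases) with substance-specific causality survey" with no exception for early stoppers. Section 6.1 asks for concluding documentation in every patient after discontinuation, with no time limit. Section 6.2 puts final documentation at 48 to 72 weeks after the start, or at end of treatment where that comes first.

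**How long patients are treated.** The Synopsis (Duration) names treatment "for 16 weeks only, in case of genotypes 2/3" with low baseline viral load and rapid response. For genotype 1 patients with prior non-response, "retreatment duration of 72 weeks is recommended".

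**What is tabulated.** In section 8.3, "adverse drug reactions are counted by frequencies using the respective preferred terms categorized according to organ systems". The one stratification named, "stratified according to the clinical relevance of the drug effect", is serious versus non-serious. No person-time, duration stratum or common observation window is stated.

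**What the tables are for.** The Synopsis and section 4.2 plan a descriptive comparison with tolerability data from clinical studies.

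**The concern.** Two features act together. First, the period in which an event can enter the database depends on how treatment ended, and the sections that define that period do not agree. With about 600 centres planned, some may stop recording at end of treatment, some at day 90 and some at week 24. An event that was never recorded cannot be recovered in the analysis.

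Second, a percentage of patients with a reaction rises with time at risk. If patients treated for 16, 24, 48 and 72 weeks are pooled in one crude frequency, the result depends on the mix of durations as well as on the drug. Setting that figure beside clinical-study data, collected over other durations and windows, confounds tolerability with treatment length. Safety is part of the main objective, so this is a central table.

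**Working it through.** The protocol gives no reaction rate, power figure or event count, so there is no stated figure to reproduce. The inputs are the 90 days (7.4), the week-24 visit (7.2.2) and the 16- and 72-week durations (Synopsis). All rates below are assumptions.

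**1. Post-treatment windows.** Week 24 is 24 × 7 = 168 days. This length is inferred from the visit schedule, since 7.4 does not state it. Section 6.1 supports it: 48 weeks of treatment + 24 = 72, its approximate documentation period per patient. Early stoppers have 90/168 = 54% of that window, a gap of 78 days (11.1 weeks).

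**2. Total windows** (treatment plus post-treatment weeks; 90 days = 12.9 weeks).
- Stop at week 12: 12 + 12.9 = 24.9 weeks
- 48-week completer: 48 + 24 = 72 weeks
- 72-week completer: 72 + 24 = 96 weeks

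**3. Unequal treatment exposure.** The range is 72/16 = 4.5-fold. Assume one constant on-treatment hazard giving 20% at 48 weeks: λ = −ln(0.8)/48 = 0.00465 per week. The crude percentage at t weeks is 1 − exp(−λt):

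| Weeks on treatment | Crude percentage |
| --- | --- |
| 16 | 7.2% |
| 24 | 10.6% |
| 48 | 20.0% |
| 72 | 28.4% |

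That is a four-fold spread with identical risk. The rate, 0.00465 × 52 × 100 = about 24 per 100 patient-years, is the same in every row.

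The spread depends on the assumed rate. At 0.05 per patient-year it is 1.5% at 16 weeks against 6.7% at 72. At 0.2 it is 6.0% against 24.2%, and at 1.0 it is 26.5% against 75.0%.

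**4. The 90-day rule by itself.** Assume a share s stops at week 12, the rest complete 48 weeks, the on-treatment rate is 0.2 per patient-year, and the post-treatment rate is f times that. A patient treated for t weeks and followed for p weeks has probability 1 − exp(−0.2(t + f·p)/52). Compare p = 12.9 with p = 24 for the stoppers, with completers at p = 24 throughout:

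| s | f | 90-day rule | 24 weeks for all | Difference (points) |
| --- | --- | --- | --- | --- |
| 0.3 | 0 | 13.15% | 13.15% | 0 |
| 0.3 | 0.1 | 13.83% | 13.95% | 0.1 |
| 0.3 | 1 | 19.67% | 20.81% | 1.1 |
| 0.5 | 1 | 16.65% | 18.56% | 1.9 |

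The last row is an extreme: half the patients stop at week 12 and reactions continue undiminished after treatment.

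**5. Effect of a common cut-off at last dose + 90 days.** The 78-day gap becomes 0. Total windows for 16-, 24-, 48- and 72-week completers become 28.9, 36.9, 60.9 and 84.9 weeks. The 4.5-fold treatment range remains, so a cut-off without person-time or duration strata would not be enough.

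**The case against.** The strongest reply is that denominators, windows and exposure-adjusted rates usually belong in a statistical analysis plan. That plan is not shown, and section 8.3 does not exclude them. Section 9 also promises to present the effect of interfering variables. This stands as a limit: nothing in the protocol prevents a better table. But 8.3 does state a summary and one stratification, and that summary is the weaker choice for this range of durations.

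The conflict over recording can also be softened. Section 7.2 says listed items need not all be investigated. Against the closure rule in 6.2, the 90-day sentence can be read as extending recording for early stoppers. That is a fair reading, and it shows that the sections need reconciling.

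The four-fold spread uses the two extreme durations. If the same hazard continued through follow-up, completers' windows would be 40 to 96 weeks and the figures 17% and 36%, about two-fold. If reactions cluster early in treatment, crude percentages differ less. The numbers are illustrations.

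A reader might infer more than the documents support:
- **That only adverse drug reactions will be reported.** Sections 8.3 and 9 promise descriptive presentation of all recorded data, and adverse events are recorded with causality.
- **That the 90-day rule seriously distorts reaction rates or hides intolerance.** Its pooled effect is small. Lack of tolerability is one of seven listed reasons for stopping, so even the direction is uncertain.
- **That a planned comparison of stoppers with completers, or of regimens, is spoiled.** None is planned. The contrast of practices with hospital departments concerns quality of treatment, and no section shows that treatment length differs between them.
- **That results are shown to be non-comparable with the clinical studies.** The windows used in those studies are not in the protocol, so confounding by treatment length is a risk of unknown size.

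**Conclusion.** The point holds in two parts of different weight. The sections on when adverse event recording ends (6.2, 7.2.2 and 7.4) do not fit together, and this follows directly from the text once the 24-week follow-up is inferred from the visit schedule. Its effect on a pooled reaction percentage is small: about 0.1 to 1.1 points with 30% stopping at week 12 and an on-treatment rate of 0.2 per patient-year.

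The larger part is the crude frequency in 8.3. With durations of 16 to 72 weeks, identical risk can appear as 7% or 28% under a constant hazard fixed at 20% by week 48. The actual size depends on the mix of durations and on when reactions occur, and the protocol gives neither. Confidence is high on the recording conflict and moderate on the analysis part, since an unseen analysis plan could already deal with it. This should be corrected, but it does not invalidate the study.

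**What to change.** 1. **Sections 6.2, 7.2.2 and 7.4:** reconcile them so that one statement says when adverse event recording ends for each kind of patient. Simply deleting the 90-day sentence is a poor remedy. Under 6.2 it could leave early stoppers with less recording. This version is dated 28.02.2013, planned last patient in was 31/12/2011, and the eCRF refuses dates older than three months (7.1), so late events could not generally be entered afterwards.
2. **Tables:** count events from treatment start to last dose + 90 days in every patient. End time at risk earlier where documentation ended earlier.
3. **Section 8.3:** for each preferred term and organ system, give the number of patients with at least one event together with the rate per 100 patient-years, or present the counts by actual treatment duration. Showing percentage and rate together guards against over-reading the rate if reactions cluster early. Strata of actual duration are formed after baseline and partly by tolerability, so they are descriptive only. Intended duration is not a usable stratum, because it is not among the listed baseline variables.

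The dates needed are planned: event start and end (7.2.8), and treatment start, dated dosing entries and an end-of-treatment record (7.2.2). The last-dose date is not named as a separate field there, so confirm that it can be derived.

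**Cost:** extra columns in the safety tables. Events in completers after day 90 leave the main table and go into a listing. No new data collection is needed for the tables.

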# Conduct of the noninterventional study

## Duration and premature termination of the noninterventional study

The noninterventional study will start on 1-Jan-2008 and is scheduled to end on 30-Jun-2014. The individual duration of the documentation of a patient is about 72 weeks.

The noninterventional study is intended to cover the entire treatment period (depending on the physician's decision and the main baseline factors such as genotype and viral load, or up to the end of treatment with peg­interferon alfa-2a (Pegasys®). Independently of the treatment decision taken, concluding documentation is to be generated for every patient even after discontinuation of treatment with peg­interferon alfa-2a (Pegasys®).

In the event of premature termination of the overall prospective noninterventional study, for example for regulatory reasons, the available data will be analyzed completed and a final report of the prospective noninterventional study will be compiled, if appropriate in a reduced form.

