## Procedure

This trial does not influence the individual course of treatment. The noninterventional study has no influence on the medical decisions and procedures. The participating physician is requested, however, to document the decisions and measures taken in the case record form of this noninterventional study.

The documents attempt to reflect the usual course of treatment as closely as possible and thereby facilitate documentation. Under no circumstances are they to be misunderstood as instructions for the management of treatment.

The documentation procedure per patient is as follows:

1. the diagnosis is made and the treatment decision is taken outside the study
2. patient informed consent
3. patient status and statement regarding start of study
4. any interim findings
5. patient status and information on treatment at end of study. The final documentation should generally be performed 48 – 72 weeks after the start of the study or at the end of the treatment, if this is sooner.

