#### At the end of treatment / documentation (end of therapy):

- Therapeutic consequence: reason for end / discontinuation of therapy
- Reasons for therapy discontinuation: lacking virological response, lacking tolerability, lacking compliance, unplanned event (e.g. imprisonment, detoxification), patient's wish, patient no longer attended, other reason
- Concomitant medication
- New comorbidities
- Body weight
- Hepatitis C laboratory diagnostic tests
  HCV-PCR (quantitative/qualitative), *only recommended in week 12*
  HCV-PCR (qualitative), *only recommended in week 24 for GT-2/3, only in week 48 for GT-1/4*
  (HCV-PCR (quantitative/qualitative) can be documented in week 4, 8, 12, 24 and 48)
- Hepatitis B laboratory diagnostic tests (only if chronic hepatitis B was documented at the baseline examination): HBsAg (+/-), HBeAg +/-; HBV-DNA quant./qual., anti-HBs (+/-); anti-HDV (+/-), HDV-RNA (+/-, qual. or quant.)
- Autoantibodies: ANA, LKM, SMA, AMA, SLA, Trak, MAK, rheumatoid factors, other
- Laboratory parameters
  GPT (=ALT), GOT (= AST), GGT,
  Other laboratory parameters:
  hemoglobin, platelets, WBC, neutrophils (%), bilirubin, creatinine, TSH, blood glucose (fasting), HbA1c, triglycerides, cholesterol, HDL, LDL, serum ferritin
- Clinical symptoms: none, fatigue, fever, muscular stiffness, skin changes, hair loss, joint pain, muscle pain, abdominal pain, nausea, reflux, weight loss, headache, insomnia, irritability, restlessness, depression, depressive mood, psychosis, impaired concentration, anorexia, jaundice, pruritus, elevated GPT, craving / withdrawal-like symptoms, other;
  causal relationship with Pegasys and/or ribavirin
- Treatment-related sick leave (duration) since the last examination
- (Monthly) pregnancy test
- Adverse events (including suspected cases) with substance-specific causality survey
- Clinical assessment of the tolerability of Pegasys and the combination with ribavirin (Copegus®): very good, good, moderate, poor
- Quality of life assessment compared to before treatment: symptom-free; improved, but not symptom-free; unchanged
- Alcohol consumption no/yes, if yes, inquiry ≤/ > 40 g/d and drinks/d in the last 30 days
- Compliance (assessed by the physician):
   very good: all medications taken
   good: max. 10% not taken
   satisfactory: max. 20% not taken
   poor: > 20% not taken
- Quality of life assessment compared to before treatment: symptom-free; improved, but not symptom-free; unchanged

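### Section 7.4 gives patients who stop treatment early a shorter adverse-event window (90 days) than the 24-week follow-up that applies in general, without a reason, and the sections on when documentation closes do not agree

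*Protocol*

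**What the plan says.** Section 7.4 (Adverse events) asks for all adverse events to be recorded, "regardless of whether they are serious or not, during the noninterventional study including the follow-up phase". The next sentence sets a different limit for one group: "For patients who discontinue the treatment prematurely, the adverse events are documented for up to 90 days after treatment discontinuation". The section gives no reason for the difference.

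Four other places bear on the window:

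- **Section 7.2.2, follow-up form.** The form is headed "To week 24 of follow-up" and lists "Adverse events (including suspected cases) with substance-specific causality survey". It does not exempt patients who stopped early. The introduction to section 7.2 presents all such items as ones that can be documented, not ones that must be.
- **Section 7.2.2, end-of-treatment form.** It records "Reasons for therapy discontinuation: lacking virological response, lacking tolerability, lacking compliance, unplanned event", and also the patient's wish, non-attendance and other reasons.
- **Section 6.1.** It says that "concluding documentation is to be generated for every patient even after discontinuation of treatment with" peginterferon.
- **Section 6.2, last step.** Final documentation is placed at 48 to 72 weeks after the start, or at the end of treatment if that comes first.

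Section 8.3 counts adverse drug reactions as frequencies by preferred term and organ system, split into serious and non-serious. It mentions neither a common observation window nor an adjustment for observation time. Section 7.2.8 has the start and end date of each event recorded.

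**The concern.** Whether a patient falls under the 90-day limit is decided after baseline, by stopping treatment early, and one listed reason for stopping is poor tolerability. The length of safety observation after treatment therefore depends on an outcome that can itself be a safety outcome. A late or persistent event on day 100 after the last dose is inside the stated window for a patient who completed treatment and outside it for one who stopped early.

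Safety is part of the main objective, and the recorded data are to be compared with the known safety profile. With plain counts, late events would be under-recorded among early stoppers, and the cohort's post-treatment total would depend partly on how many patients stopped early.

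There is also a practical problem. A site that follows section 7.4 stops recording at day 90. A site that works from the follow-up form asks again at week 24. A site that reads section 6.2 literally may close the file at the end of treatment. Differences between sites in late events could then reflect which section each one followed.

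**Working it through.** The protocol gives no figure for the effect of the two windows, so there is none to reproduce.

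**Inputs from the protocol.** Window for early stoppers: 90 days (section 7.4). General window: the follow-up phase (section 7.4), which runs to week 24 (section 7.2.2).

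**Window length.**

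- General: 24 × 7 = 168 days
- Difference: 168 − 90 = 78 days
- Relative shortfall: 78 / 168 = 46.4%; early stoppers keep 90 / 168 = 53.6%

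**Share of post-treatment events missed in early stoppers.** This depends on how fast the event rate falls after stopping, which the protocol does not give. Assume an exponential decline with half-life h and set k = ln 2 / h. Of the events that would occur in 168 days, the share missed is

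1 − (1 − exp(−90k)) / (1 − exp(−168k)).

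For h = 30 days, exp(−90k) = 0.125 and exp(−168k) = 0.0206, so the share is 1 − 0.875 / 0.9794 = 10.7%. The other values follow in the same way:

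| Assumed half-life of the event rate | Share missed |
| --- | --- |
| 14 days | 1.1% |
| 30 days | 10.7% |
| 60 days | 24.5% |
| 90 days | 31.1% |
| 180 days | 38.5% |
| constant rate | 46.4% |

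**Effect on the cohort's post-treatment count, upper end.** Assume a constant rate, equal post-treatment risk in both groups, and a share s of early stoppers. The fraction captured is s × 90/168 + (1 − s).

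- s = 10%: 0.954, a loss of 4.6%
- s = 20%: 0.907, a loss of 9.3%
- s = 40%: 0.814, a loss of 18.6%

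The protocol states no discontinuation rate, so these values of s are illustrations. A falling event rate makes the losses smaller. Events during treatment are not affected, so the effect on a total that includes them is smaller again.

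**How much a text change can still recover.** This version is dated 28.02.2013, and the last patient was planned in by 31/12/2011. The interval is 366 + 59 = 425 days. A patient who started on that last date would already be past day 90 after stopping if treatment ended before day 425 − 90 = 335, about week 48. For most early stoppers the 90 days had therefore run out before this version was issued.

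**The case against.** **The sentence may be harmless, or even lengthen observation.** Section 6.2 allows documentation to close at the end of treatment. For a patient closed that way, 90 days adds observation. This stands as far as it goes, and it also means one cannot say that everyone else is followed for 24 weeks. But section 7.4 words the 90 days as an upper limit, and a reading as a minimum would itself need a correction.

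**The follow-up form does not contradict section 7.4.** A reader might infer a direct conflict. Section 7.2 makes the form's items optional, so an available field can coexist with a specific rule elsewhere. What remains is an ambiguity that sites can resolve differently.

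**Early stoppers need not be the most harmed.** A reader might infer that the patients with most harm get the least observation. The documents do not support that. Intolerability is one reason among several, no shares are given, and the synopsis itself describes stopping after week 12 for lack of early virological response. What holds is that intolerability is among the reasons.

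**46% is not the share of events lost.** It is the difference in window length. It becomes an event loss only under a constant rate for 24 weeks after stopping, which is hard to defend for drug reactions, and only for post-treatment events in early stoppers. Patients who no longer attend may supply nothing after day 90 under any rule.

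**The affected comparisons are mostly not planned.** The protocol announces no comparison of adverse events between completers and early stoppers, and its contrast of practices with hospital departments concerns quality of treatment. This stands. The comparison with the known safety profile is planned.

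**Serious events.** A reader might infer that serious events after day 90 in early stoppers escape expedited reporting. Section 7.5 ties reporting to events documented as adverse events but sets no time limit of its own, so the text leaves this open and does not establish a gap.

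**A single window does not equalise observation.** Treatment length still differs between patients, and exposure adjustment is a matter for the analysis plan, which is not shown. Both are true. The change removes the difference in post-treatment recording only.

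**Conclusion.** The point holds in a limited form. Section 7.4 sets a post-treatment adverse-event window that is up to 78 days (46%) shorter for patients who stop early, gives no reason, and does not fit cleanly with the follow-up form or with sections 6.1 and 6.2. Because the window depends on a post-baseline outcome that includes intolerability, and section 8.3 counts plain frequencies, late events in that group would be under-recorded.

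The window difference rests on the protocol alone and assumes that the other patients do reach follow-up week 24. The event loss rests on assumed rates: from about 1% at a 14-day half-life to at most 46% at a constant rate, in early stoppers' post-treatment events only. Severity is moderate: the planned analysis is descriptive, on-treatment events are untouched, and the likely loss for quickly resolving reactions is small.

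**What to change.** 1. In section 7.4, replace the 90-day exception with one documentation window for all patients: to follow-up week 24 after the end of treatment, whatever the reason for stopping. Reconcile sections 6.1, 6.2 and the follow-up form in 7.2.2 with it. If the 90 days was intended, state why and say how the analysis deals with it.
2. For records already closed at 90 days, add a table of post-treatment events with onset up to day 90 in all patients, built from the recorded start dates, and show it beside the full-window table. Completers' later events then stay visible. Given the date of this version, this table does most of the work.

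The cost is slightly more documentation for early stoppers still under observation, a few sentences of protocol text and one extra table. The follow-up form already carries the item. The change concerns documentation only, not treatment, and on-treatment time will still differ between patients.
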